| Homed-based pulmonary rehabilitation (video-assisted)                                                                                                                                                                                                                                                                                                                                                              |                                                                                                                                                                                                                                                                                                                   | Pulmonary tele-rehabilitation                                                                                                                                                                                                                                                                                                                                                                                                                                                                                                                                                                                                                                                                     |                                                                                                                                                                                                                                                                                                     |
| Topic/themes                                                                                                                                                                                                                                                                                                                                                                                                       | Communication/ learning form                                                                                                                                                                                                                                                                                      | Topic/themes                                                                                                                                                                                                                                                                                                                                                                                                                                                                                                                                                                                                                                                                                      | Communication/ learning form                                                                                                                                                                                                                                                                        |
| 
 
- COPD and treatment
 
- Importance of smoking cessation
 
- Importance of daily physical activity and exercise
 
- Importance of nutrition
 
- Medication and use of devices
 
- Early signs of exacerbation and action plan
 
- Use of nebulizer apparatus and oxygen apparatus
 
 (duration 60 min once a week) | Topics/themes of patient choice discussed during phone call: 
 
- Information
 
- Dialogue
 
- Reflection exercises
 
- Practical exercise
 
- Focus increasing individual self-competences
 
- network and sharing experiences
 
 | 
 
- COPD and treatment
 
- Importance of smoking cessation
 
- Importance of daily physical activity and exercise
 
- Importance of nutrition
 
- Medication and use of devices
 
- Early signs of exacerbation and action plan
 
- Use of nebulizer apparatus and oxygen apparatus
 
- Repetition and group needs
 
 (duration 3 x 20 min/week) Every second session is mindfulness exercises 
 
-Awareness of heartbeat and bloodflow
 
-Awareness of the body
 
-Awareness of sounds and thoughts
 
-Mindfull stretch
 
 | Topics/themes promoted as a combination of: 
 
- Information
 
- Dialogue
 
- Reflection exercises
 
- Practical exercise
 
- Focus on increasing individual self-competences
 
- network and sharing experiences
 
 |
| Self-initiated by patient and phone discussions weekly with HCP (RN/PT)                                                                                                                                                                                                                                                                                                                                            |                                                                                                                                                                                                                                                                                                                   | Health professional responsible: Respiratory nurse                                                                                                                                                                                                                                                                                                                                                                                                                                                                                                                                                                                                                                                |                                                                                                                                                                                                                                                                                                     |

## Appendices 2

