## **2.1 Objectives and hypotheses**

**2.1.1 Primary objective (RCT- study I)** of the REPORT study is to evaluate the effects of structured home-based pulmonary rehabilitation (HPR) and supervised pulmonary tele-rehabilitation (PTR) on respiratory symptoms, quality of life, functioning and physical activity in patients with moderate to severe COPD who are unable or unwilling to access the conventional hospital- and community-based PR programs.

**2.1.2 Our hypotheses** are that HPR and PTR will lead to respiratory symptom relief in the patients and that PTR and HPR will be equivalent to each other and superior to usual care, that is the a control group (CON - no intervention) among patients unable to access conventional rehabilitation programs.

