## **3.7 Interventions (also read figures in appendices 1)**

### **3.7.1 Pulmonary Tele-Rehabilitation (PTR)**

The PTR intervention is supervised by skilled physiotherapists and respiratory nurses with at least 2-years of substantial experience with PR and delivered via a virtual platform at Bispebjerg and Hvidovre Hospital to a group of 4–6 patients who exercise at home and communicate via tablet with Center for IT and Medico (CIMT) approved communication software. Each session is 60 min; 35 min of exercise and 25 min of patient education, two times per week for the duration of 10 weeks. The specific exercises used are evidence-based as they have been used in several intervention studies on patients with severe or very severe COPD and involves larger muscle groups with 50/50% exercises for upper and lower extremities, respectively. Volume, intensity and content specified for the exercise protocol is in accordance with both national and international exercise recommendations. The exercise sessions include relative progression every fourth week, as the patients are expected to improve their mental and physical capacity during the intervention. Additionally, to the supervised program, patients are instructed to do daily physical activity of at least 30 minutes by modalities accessible to the patient, e.g. in- or outdoor walking activities in bouts of minimum 10 minutes.

Every second session of the patient education consists of 25 minutes of Mindfulness-based Cognitive Therapy (MCBT) exercises and education developed for COPD patients with the potential mediating effects of mindfulness, self-compassion and breathlessness catastrophizing. The other education sessions consist of dialogue reflections around empowerment of the subjects: action-plan for symptom deterioration, medication-technic and correct use, better living with COPD, nutrition and importance of smoking cessation.

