### **3.7.3 Control**

Patients randomized to the control group will receive usual care; medication, scheduled follow-up visit and possible phone contact with GP or the outpatient respiratory department. Except for assessment visits 10-, 35-, and 75-weeks from baseline no intervention is offered.

If a patient changes his/her mind and wishes to participate in a conventional hospital- or community-based PR program, it will be granted as this is a highly recommended treatment (e.g. rehabilitation after hospital admitted exacerbation).

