### **3.7.4 Maintenance**

During the 15-month maintenance program, patients are asked to continue at home with a similar program to that completed. The weekly goal is for the patient to achieve at least 30 minutes of self-initiated muscle-endurance based exercises twice weekly, complete a mindfulness program of choice for 15 minutes at least once a week and, in addition they are once weekly offered healthcare professional (physiotherapist/nurse) supervised exercise (groups of 4-6 persons), mindfulness and dialogue/consultation for 60 minutes throughout the 15-month maintenance period.

The prescribed physical exercises are available on the tablet as an instructed exercise-film. Seven mindfulness exercises are available from sound-files on the tablet for self-initiated mindfulness-guidance.

The overall goal for the maintenance program is that the patient achieves sustainable exercise habits and maintain or even improve gains from the intervention.

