| 'First patient inclusion'                                                    |      |    |    |    |      |    |    |    |      |    |    |    |      |    |    |    |
| Recruitment and randomization                                                |      |    |    |    |      |    |    |    |      |    |    |    |      |    |    |    |
| Intervention                                                                 |      |    |    |    |      |    |    |    |      |    |    |    |      |    |    |    |
| Maintenance intervention and follow-up data collection                       |      |    |    |    |      |    |    |    |      |    |    |    |      |    |    |    |
| Dissemination – Conferences                                                  |      |    |    |    |      |    |    |    |      |    |    |    |      |    |    |    |
| Dissemination – stakeholders' workshop                                       |      |    |    |    |      |    |    |    |      |    |    |    |      |    |    |    |
| International collaboration abroad                                           |      |    |    |    |      |    |    |    |      |    |    |    |      |    |    |    |
| Post doc – [name]                                                     |      |    |    |    |      |    |    |    |      |    |    |    |      |    |    |    |
| Post doc project – Rethink pulmonary rehabilitation and maintenance programs |      |    |    |    |      |    |    |    |      |    |    |    |      |    |    |    |

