| Control group       | 
 
• Patients randomized in the control group will receive usual care; medication, contact and scheduled controls for the first 10 weeks. After 10 weeks, controls will be offered to participate in the maintenance exercise program for 15-month (65-weeks) free of charge or to continue as control without maintenance. The 10-, 35- and 75-weeks follow-up from baseline is the same as the intervention groups. If a patient changes their mind and wish to participate in a conventional hospital- og community-based PR program, it will be granted since this is a high recommended treatment (e.g. rehabilitation after hospital admitted exacerbation).
 
                                                              |
| Maintenance program | 
 
• During the 15-month maintenance program, patients are asked to continue at home with a similar program to that completed in the intervention twice weekly with tablet and exercise equipment available and they are additionally offered group supervised exercise, mindfulness and dialogue/consultation (physiotherapist/nurse) once weekly for 60 minutes throughout the 15-month maintenance period. The overall goal for the patient is to achieve sustainable exercise habits and maintain or improve gains from the intervention.
 
                                                                                                                                                                                   |

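### Section 3.7.3 offers controls no intervention through week 75, but Appendix 1 offers them the 65-week maintenance programme after week 10, so the comparator for the later contrasts is contradictory

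*Protocol*

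**What the plan says.** Section 3.7.3 gives controls usual care and adds: "Except for assessment visits 10-, 35-, and 75-weeks from baseline no intervention is offered". It makes one exception: a control who asks for conventional rehabilitation will get it.

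The control row of the intervention table in Appendix 1 describes "usual care; medication, contact and scheduled controls for the first 10 weeks". It continues: "After 10 weeks, controls will be offered to participate in the maintenance exercise program for 15-month (65-weeks) free of charge". The same sentence lets the patient choose to remain a control without maintenance. It then repeats the exception for conventional rehabilitation.

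Section 3.7.4 describes what is on offer. Besides exercise and mindfulness at home, patients are "once weekly offered healthcare professional (physiotherapist/nurse) supervised exercise (groups of 4-6 persons), mindfulness and dialogue/consultation for 60 minutes throughout the 15-month maintenance period".

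Section 2.1.2 states the hypothesis that both rehabilitation models will be "superior to usual care, that is the a control group (CON - no intervention"). Section 3.6.1 plans mixed-model analyses of group differences at weeks 10, 35 and 75 by intention to treat, and chi-squared comparisons of hospitalisation and death. Section 2.1.3 follows admissions, length of stay and mortality from baseline throughout follow-up. Section 3.2 sets the primary endpoint at week 10 and calls week 75 the primary endpoint of the maintenance study.

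**The concern.** A reader cannot tell what the control arm is offered from week 10 to week 75. Under section 3.7.3, a later contrast with control sets rehabilitation plus maintenance against usual care. Under Appendix 1, it sets rehabilitation plus maintenance against 10 weeks of usual care followed by optional access to the same maintenance programme. These are different questions, and they can have different answers.

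If Appendix 1 governs and some controls join and benefit, the later contrasts shrink. A small difference at week 75 could then be read as a fading benefit of rehabilitation when it reflects treatment in the control arm. The opposite error is also possible: a result obtained under Appendix 1 could be reported as a comparison with no intervention, because that is how the hypothesis describes the control group.

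Which treatment an arm is offered is for the protocol to decide. A statistical analysis plan can say how to interpret the contrast, but it cannot decide what the sites deliver.

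**Working it through.** No planned figure is in dispute, so the check is mainly a comparison of texts.

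1. **Period covered.** Section 3.7.3 names the assessment visits at weeks 10, 35 and 75 as the only exceptions to offering nothing, so its statement runs to week 75. Appendix 1 confines the usual-care-only period to the first 10 weeks. The two agree up to week 10 and part after it.

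2. **Does maintenance count as an intervention?** It is section 3.7.4, under the general heading for interventions, and a row of the project timeline is labelled "Maintenance intervention and follow-up data collection". In content it is active treatment: a weekly 60-minute supervised group session, plus exercise and mindfulness at home.

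3. **Does the main text extend maintenance to controls?** No. Section 3.7.4 describes carrying on with a programme like the one already completed. Controls have completed none, so the section does not supply the missing offer.

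4. **What the two texts share.** Both grant conventional rehabilitation on request. That is consistent and not part of the conflict, which concerns the maintenance offer alone.

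5. **Share of follow-up affected.** Last visit at week 75 and offer at week 10: 75 − 10 = 65 weeks, which matches the 65-week length in Appendix 1. The share is 65/75 = 0.867, or 87%.

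6. **Analyses affected.** These are the contrasts with control at weeks 35 and 75 in section 3.6.1, and admissions, length of stay and mortality, which accrue over the whole period.

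7. **Analyses not affected.** The three primary comparisons use the week-10 outcome, before any offer. Home-based versus tele-rehabilitation does not involve the control arm at any visit.

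**The case against.** The best counter-argument is about vocabulary. Much of the protocol keeps intervention and maintenance apart. Section 3.2 has a 10-week intervention followed by self-maintenance; section 3.5.3 calls them phases 1 and 2; Table 1 labels week 10 as the end of intervention and the later visits as maintenance; and the timeline gives them separate rows. On that usage, section 3.7.3 could mean only that controls get neither of the two rehabilitation models. The heading of section 3.7, "3.7 Interventions (also read figures in appendices 1"), also sends the reader to Appendix 1, which could then be read as elaboration. This lessens the conflict but does not remove it. A statement meant only for the 10-week programmes had no need to name weeks 35 and 75, and even on the kinder reading section 3.7.3 omits a treatment offer that spans 65 weeks.

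It is also fair to say that the hypothesis in section 2.1.2 belongs mainly to the randomised trial with its week-10 primary endpoint, and that the maintenance aim in section 2.1.3 names no control comparator. The problem is therefore confined to long-term contrasts. It is still real there, because section 3.6.1 plans group differences at weeks 35 and 75 and the registry outcomes are listed as aims of the randomised trial.

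Three stronger readings are tempting, and the documents do not support them.

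- A reader might infer that controls are offered more supervised treatment than the tele-rehabilitation arm, whose sessions of 60 minutes run "two times per week for the duration of 10 weeks" (10 × 2 × 60 min = 20 h), against 65 × 60 min = 65 h of maintenance. But tele-rehabilitation patients are offered the same maintenance, so the totals are 20 + 65 = 85 h against 65 h.
- A reader might want to put a figure on the loss of power at week 75. That would need uptake among controls, their benefit, and a week-75 difference and standard deviation. The protocol gives none of these, and its 2.5 and 4.5 were set for the primary outcome at week 10.
- A reader might conclude that the later contrasts are invalid. They are not: arms compared as randomised remain a valid comparison of strategies. What fails is the description of the comparator as no intervention.

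**Conclusion.** The inconsistency holds. Section 3.7.3 and Appendix 1 give different control conditions after week 10, and no text reconciles them. It affects the comparator for the week-35 and week-75 contrasts with control and for admissions, length of stay and mortality, over 65 of 75 follow-up weeks (87%).

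This rests on reading section 3.7.3 as covering the maintenance period, which its reference to weeks 35 and 75 supports. Any shrinkage of the later contrasts is conditional: it requires that Appendix 1 governs, that controls take up the programme, and that they benefit. Its size is unknown.

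Offering rehabilitation to controls after the primary endpoint is not criticised here. The point is worth correcting because it is cheap to settle and bears on how the long-term results will be read.

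**What to change.** State one post-week-10 control condition, in the same terms, in section 3.7.3 and in Appendix 1.

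If controls are to receive no offer, delete it from Appendix 1. If the offer stands:

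- limit the claim of superiority to usual care or no intervention (section 2.1.2) to week 10;
- describe the week-35 and week-75 contrasts with control, and those for admissions, length of stay and mortality, as immediate rehabilitation plus maintenance versus 10 weeks of usual care followed by optional maintenance;
- report how many controls took up maintenance, from the adherence records in Table 1, and how many received other rehabilitation, from the registry data in section 3.5.2.

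Both data items are already planned, so the cost is a protocol clarification with no new data collection. The offer need not be withdrawn. The downside of keeping it is a narrower long-term claim against control.

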### *Fysisk præstations målinger:*

#### 1. 30sec- sit-to-stand-test (30STS) (Jones CJ et. 1999) (standard test i Lunge-rehabilitering)

30-sec sit-to-stand test (30sec-STST) er en indirekte måling af muskelstyrke af benene.

Testen udføres fra en stol med ryglæn og en sædehøjde svarende til 45-47 cm. Deltageren blive instrueret i at rejse og sætte sig så mange gang som muligt på 30 sekunder med armene krydset over brystet. Antal gennemførte rejse og sætte sig bliver registeret. Scoren "nul repetitioner" skrives hvis en patient ikke kan gennemføre testen (dvs. rejse-sætte-sig fra en stol uden brug af arme/hænder). Testen gentages to gange for at indfange evt. læringseffekt. Der holdes en pause på 5-minutter imellem de to forsøg. Det bedste testresultat anvendes. Testen anvendes som **standard test i Lunge-rehabilitering og i ambulant medicinsk behandling.**

#### 2. Udholdenhed – 6 min walking test (6MWT) (ERS/ATS technical guideline 2014) (standard test i Lunge-rehabilitering) OBS! Den test gennemføres kun på de patienter som vælger at få udført undersøgelse på hospitalerne.

6-minute walk test (6MWT) anvendes til måling gang udholdenhed og gang kapacitet. Testen er anses som GOLD standard gang test i lungemedicin og anvendes som effektmål i lungerehabilitering og den danske regioners kvalitetsdatabase (RKKP-DRKOL). Gangtesten gennemføres på en 20 meter lang gangbane. Patient instrueres i at gå så langt som muligt på 6-minutter, og modtager undervejs standardiserede opmuntring fraser. Testen gennemføres to gange med 30 minutters pause imellem for at eliminere læringseffekt. Det bedste testresultat anvendes. Testen anvendes som **standard test i Lunge-rehabilitering og i ambulant medicinsk behandling.**

